**Fig. 2 fig2:**
[figure not shown]
Overview of the assessment procedures (PAREMO-20, Patient Questionnaire for Assessment of Rehabilitation Motivation. SIBAR, Screening Instrument for the subjective need for Occupation related Rehabilitation. SFI, Spine Functional Index. FREM-8, Questionnaire for assessing Rehabilitation related Expectations and Motivations. ODI, Oswestry Disability Index. SF-12, 12-Item Short-Form Health Survey. EMG, Electromyography. COP, Center of pressure).

**Table 2 tbl2:** Experimental outcome categories with exploratory variables.

Outcome categories	Explanatory variables	Unit or range
Resting heart function	Heart rate	bpm
	Heart rate variability (RMSSD)	ms

Resting muscle tone	Oscillation frequency	Hz
	Dynamic stiffness	N/m
	Logarithmic decrement	–
	Mechanical stress relaxation time	ms
	Ratio of relaxation and deformation time	–

Reach distance	Unloaded distance	cm
	Loaded distance	cm

Handgrip strength	Absolute strength	kg
	Relative strength	kg/kg

Standing balance control	COP path length	mm
	COP average velocity	mm/s
	95% confidence ellipse area	mm^2^
	Forefoot average force L	%
	Total average force L	%
	Muscle activation coefficient of variability	%
	Muscle activation symmetry	%
	Glutaeus medius coactivation	0–1

Gait control	Gait velocity (self-selected)	km/h
	Stride length	cm
	Step length L	cm
	Step length R	cm
	Step width	cm
	Stride time	s
	Step time L	s
	Step time R	s
	Cadence	steps/min
	Heel maximum force L	N
	Heel maximum force R	N
	Heel maximum force symmetry	%
	Muscle activation coefficient of variability	%
	Muscle activation symmetry	%

RMSSD, Root Mean Square of Successive Differences. COP, Center of pressure. L, Left. R, Right.

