### Study participants

2.2

The study participants are at least 18 years old. An overview of the inclusion and exclusion criteria is given in Table 1. Patients suffering from LSS will undergo surgical intervention or conservative treatment with a standardized rehabilitation program at the same rehabilitation center for three weeks (15 intervention sessions each lasting 4 to 5 h). LSS patients will be recruited and treated in two local but independent spinal surgery centers. The conservatively treated group will be enrolled at the rehab center. Patients meeting the inclusion criteria listed in Table 1 will be included consecutively in the study. Control participants will be recruited through public announcements. Furthermore, patients will be encouraged to recruit controls without any known lumbar spinal impairments of approximately the same age, sex, and activity status from their own environment.

**Table 1 tbl1:** Inclusion and exclusion criteria for the patients.

Inclusion criteria	Exclusion criteria
- Age: at least 18 years old - Voluntary participation - Signed consent - Anatomical lumbar spinal stenosis with characteristic symptoms - Present pain (NRS >3) - Agreement to be treated in the selected rehabilitation facility	- Children and adolescents - Neurodegenerative diseases - Previous spine surgery - Fractures on the lumbar spine (<2 years) - Degenerative lumbar scoliosis (>20°) - Spondylolisthesis > Meyerding 1 (3–14 mm) - ASA classification [18] >4 - Pain (NRS <3) - Orthopedic history at the lower extremities, limiting the patient's activity

For representative sampling, the study collective is self-monitored with regard to the proportion of females included, the preferred post-operative rehabilitation timing, and other parameters that may need to be balanced in periodic meetings of the participating study centers.

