Before functional, balance and gait analyses, patients’ heart rate variability (HRV) will be examined while lying prone to record autonomic nerve activity. After 5 min rest or relaxation time, 5 min of continuous HRV recording will be performed [28]. This will be followed by measurements of the lumbar resting myofascial tone [[29], [30], [31]] with a portable device (MyotonPRO, Myoton AS, Tallinn, Estonia) applied paravertebral at both sides to detect changes in muscle stiffness during the observation period. Thereafter, the following functional assessments will be completed by each participant: functional reach test (FRT), loaded reach test (LRT), handgrip strength, standing balance control (60s in natural position), and gait analysis on an instrumented treadmill (h/p/cosmos sports & medical gmbh, Nussdorf-Traunstein, Germany) with an integrated pressure measuring platform (FDM-THQ-i3, zebris Medical GmbH, Isny, Germany). Patients will be asked to walk at A) 2.5 km/h for approximately 30s, B) self-selected speed as long as possible or up to 6 min (6-min walk test [[32], [33], [34]]) and, after a sufficient break, C) 115% of the self-selected speed again for approximately 30s. Following each walking task, as well as after each functional test performed, patients will be asked to indicate their individual exertion (rate o perceived exertion, RPE [35]) on an 11-point NRS [36]. For an overview of the assessment procedures used in the study, please refer to Fig. 2. The ODI together with the distance walked at self-selected speed were selected as primary outcome measures, whereas strength (handgrip strength) and functional mobility (FRT) served as secondary outcomes. The experimental outcome categories with exploratory variables are listed in Table 2.

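### Table 2 lists heel maximum force only in newtons, so in the non-randomised group comparisons it partly reflects body mass; a body-weight-relative form should be added

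*Protocol article*

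**What the plan says.** Table 2 (section 2.3.1 of the protocol article) lists the experimental outcome categories.

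- **Heel force.** The gait block contains "Heel maximum force L" and "Heel maximum force R N", both in newtons, followed by "Heel maximum force symmetry" in per cent. No version of the two force rows relative to body weight is listed.
- **Handgrip.** The same table gives absolute strength in kg and also "Relative strength kg/kg".
- **Walking conditions.** Section 2.3.1 describes three treadmill walks. The first is at fixed speed: "Patients will be asked to walk at A) 2.5 km/h for approximately 30s". The second is "B) self-selected speed as long as possible or up to 6 min". The third is at 115% of the self-selected speed, again for about 30 s. In Table 2 only "Gait velocity (self-selected)" names a condition.
- **Groups.** Section 2.2 seeks "controls without any known lumbar spinal impairments of approximately the same age, sex, and activity status"; body mass is not named. Under section 2.3.8, surgical patients who decline randomisation choose early or delayed rehabilitation themselves. Section 2.3.7 (b) compares two surgical groups, the conservative group and controls.
- **Status.** The primary outcomes are ODI and distance walked at self-selected speed; the secondary outcomes are handgrip strength and the functional reach test. The Table 2 gait variables are exploratory.
- **Anthropometry.** Section 2.3 includes anthropometric measurements in the medical check-up.

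**The concern.** Vertical force under the heel is roughly body weight multiplied by a loading factor, and only the loading factor describes how the person walks. Two groups with the same gait but different mean mass will differ in newtons. The table recognises this for handgrip but not for heel force. Where neither randomisation nor matching protects against a difference in mass, a reader cannot separate loading from weight in a raw-newton comparison.

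A smaller, related point concerns speed. Stride length, step and stride times and cadence are tied to walking speed by definition, and the Background says that LSS patients walk more slowly. Three walks are recorded, but apart from velocity the gait rows do not say which walk they come from. Values from the self-selected walk and from the 115% walk would carry the difference in chosen speed.

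**Working it through.** The article gives no heel-force, body-mass or walking-speed data and no figure of its own to reproduce on this point. The numbers below illustrate size under stated assumptions.

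**Model.** Heel force F = k × m × g, with m the body mass, g = 9.81 m/s² and k the heel loading as a fraction of body weight. Assumed range: k = 0.5 to 0.7.

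**1. Between groups with identical gait.** The difference is ΔF = k × Δm × g.

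| Mean mass difference | k = 0.5 | k = 0.6 | k = 0.7 |
|---|---|---|---|
| 5 kg | 24.5 N | 29.4 N | 34.3 N |
| 10 kg | 49.1 N | 58.9 N | 68.7 N |

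Relative to a group averaging 80 kg, 5 kg is 5/80 = 6.25% of the force, whatever k is.

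**2. How much of raw force is mass?** Assume that mass and k vary independently between people, with a coefficient of variation (CV) of 15 to 20% for mass and 10 to 20% for k. Then CV²(F) = (1 + CV²(m)) × (1 + CV²(k)) − 1, and the share due to mass is CV²(m) / CV²(F).

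- Lowest share: 0.15² / (1.0225 × 1.04 − 1) = 0.0225 / 0.0634 = 35%. The share due to k is then 0.04 / 0.0634 = 63%.
- Highest share: 0.20² / (1.04 × 1.01 − 1) = 0.04 / 0.0504 = 79%. The share due to k is then 0.01 / 0.0504 = 20%.

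Raw force is therefore a mixture: mass matters a good deal, but loading information remains.

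**3. Within one patient.** With stable mass, m is the same at both visits and a change in F is a change in k. A 2 kg change gives 0.5 × 2 × 9.81 = 9.8 N to 0.7 × 2 × 9.81 = 13.7 N, which is 2/80 = 2.5% at 80 kg.

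**4. Symmetry.** Take k = 0.60 left and 0.54 right, with the index defined as the difference over the mean of the two sides: (0.60 − 0.54) / 0.57 = 10.5%. Mass cancels, and the result is the same at 60, 80 and 100 kg.

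**5. Scaling.** F / (m × g) = k, so the percentage of body weight removes mass under this model.

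**6. Speed.** Stride length = speed × stride time. At an assumed stride time of 1.2 s:

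- 2.5 km/h: 2.5 / 3.6 × 1.2 = 0.83 m
- 3.5 km/h: 3.5 / 3.6 × 1.2 = 1.17 m

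At a fixed 2.5 km/h this source of difference is absent.

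**The case against.** The strongest reply is that Table 2 lists variables and units, not models. A reader might infer that heel force will be analysed in raw newtons without adjustment, but nothing in the article says so. Section 2.3.7 (a) names only ODI, SF-12, handgrip strength and the functional reach test, and (b) to (d) speak of subjective and functional measures in general. Covariates may be set out in a full protocol or analysis plan that is not shown. This stands. What remains is that the article itself fixes the unit of these two rows and, unlike for handgrip, lists no relative form.

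A reader might also infer that group and visit differences would show body mass and chosen speed instead of gait control. The article does not support that either. Loading still contributes to raw force, mass largely cancels within patients of stable weight, randomisation balances mass in expectation among patients who accept it, and a mass-free symmetry index is already listed. Imbalance between the other groups is possible but not established. Section 2.2 provides for periodic monitoring of parameters that may need balancing, although it does not name mass.

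On speed, the assessment already includes a fixed 2.5 km/h walk, and no row except velocity is tied to the self-selected one. It would be wrong to assume that the other rows come from that walk. The gap is one of labelling.

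**Conclusion.** The point holds as a minor one. As listed, left and right heel maximum force would partly reflect body mass in comparisons of surgical, conservative and control groups, and among preference patients in early versus later rehabilitation. Under the proportional model with k between 0.5 and 0.7, each 5 kg of difference in mean mass adds about 25 to 34 N. Under the assumed CVs, mass accounts for about 35 to 79% of between-person variance in raw force. These sizes rest on assumed inputs and on independence of mass and loading; the article supplies none of them. Symmetry, and within-patient change at stable weight, are largely unaffected. The missing walk label is a secondary matter of clarity. Because the variables are exploratory, no primary or secondary conclusion changes.

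**What to change.** In Table 2, report left and right heel maximum force as a percentage of body weight, alongside or in place of newtons, or state that comparisons of these rows adjust for body mass. Use the anthropometry already collected, with mass taken at the same visit.

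As a minor addition, state for each gait variable whether it comes from walk A (fixed 2.5 km/h), B (self-selected) or C (115% of self-selected). Where B or C values are compared between groups or visits, show the walk A value alongside or adjust for speed. B and C need not be demoted to descriptive use.

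The cost is slightly more analysis work and no new test, provided that mass is recorded at each visit. Walk A lasts only about 30 s, so it yields fewer strides, and it gives no value for patients who cannot walk at 2.5 km/h.

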#### Functional reach test (FRT)

2.3.2

The unloaded FRT quantifies participants' dynamic in-place standing balance control as reach distance. The participant is standing with feet hip-width next to a wall (without touching the wall) with the right arm extended and parallel to the floor. A tape is mounted on the wall at the participant's shoulder height. The starting point is marked before the patient performs symmetrical hip flexion by moving the trunk forward without moving the feet off the ground, bending the knees, and losing balance, i.e., stepping. The distance between the starting and maximal forward reach distance beyond the participant's arm length represents the reach distance [37] and is recorded in centimeters. After two familiarization trials, three measurements will be documented. The best of three attempts will be used for further analyses. The test-retest reliability of the FRT has been found to be good to excellent with intraclass correlation coefficient (ICC) values above 0.80 [37,38]. Despite the fact that participants are required to maintain a neutral trunk position, spinal mobility has been shown to significantly affect the reach distance [39].

#### Loaded reach test (LRT)

2.3.3

The LRT was inspired by the FRT and controlled spinal loading experiments on patients with low back pain [40]. It basically aims to load the posterior chain while extending both arms and leaning forward. The participant holds an additional weight with both hands. Depending on the participant's body mass, weights with two (<70 kg), three (60–80 kg) or four (>80 kg) kilograms are used [41]. The reach distance is determined according to the FRT. After two familiarization trials, three measurements will be recorded. The test-retest and inter-rater reliability of the LRT has been found to be excellent in participants with and without low back pain [42].

#### Handgrip strength measurement

2.3.4

Handgrip strength will be measured seated at patients’ dominant side using a handheld dynamometer (SH5001, Saehan Corporation, Masan, South Korea). The position of the upper extremity is with the shoulder adducted and neutrally rotated, elbow flexed at 90° and forearm in neutral. Two maximum attempts will be recorded after two submaximal familiarization trials. For all participants, the second handle position will be used, as this is supposed to be the most reliable and consistent grip widths in adults [43]. The test-retest reliability of the handgrip strength testing in young adults during sitting has been found to be excellent, with ICC values above 0.9 [44].

#### Follow-up

2.3.5

Follow-up assessments will be performed at six, 12 and 24 months after completing the rehabilitation program.

#### Power analysis and sample size considerations

2.3.6

The ODI was set as our primary outcome measure. For this study, we approximated the sample size using a hypothetical approach. In order to estimate the number of cases needed, the ODI results of 46 patients with LSS (41% men) who underwent fusion surgery were used [45]. Considering the mean change from baseline of 16.1 points and the standard deviation of 17.8, a large effect (d = 0.9) can be expected. With a significance level of 5% and a power of 95%, the minimum sample size needed with this effect size is 15 patients with LSS who will undergo fusion surgery [one-sample *t*-test] (G*Power 3.1.9.2). Only 65% (30) of the patients reduced their ODI by at least ten points one year post-operatively [45]. Taking into account that approximately two-third of the patients included will reach the minimum clinically important difference and assuming a relatively high dropout rate of 20%, 30 patients with LSS would have to be initially included in each group.

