## Abstract

**Background:**

Patients affected by lumbar spinal stenosis (LSS) suffer from a multifactorial degeneration of the lumbar spine resulting in narrowing of the neuroforamina and spinal canal, leading to various functional limitations. It remains unclear whether LSS patients after surgery would benefit from early post-operative rehabilitation, or if a delayed rehabilitation would be more advantageous. The purpose of this partially randomized patient preference trial is to evaluate the impact of post-operative rehabilitation timing as well as surgical intervention type on psychometric properties and functional outcomes in patients with LSS.

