#### Statistical analyses

2.3.7

The data collected will be used to answer various research questions. Hence different analyses will be conducted. First, data quality checking will be performed to ensure that discrepancies, errors, or duplicates are excluded from further analyses and overall data consistency is given. Second, data will undergo exploratory data analysis. Finally, depending on the variables available, appropriate statistical tests (e.g., linear regressions, Student's t-tests, Chi^2^-tests) will be applied to uncover differences related with rehabilitation timing after LSS surgery. Statistical analyses will be performed using IBM SPSS 28.0 (IBM Corp., Armonk, NY, USA) software.a)Subjective (ODI, SF-12) and functional performance (handgrip strength, FRT) of early and later post-operative rehabilitation intervention groups will be compared using multivariate general linear mixed model and Chi^2^-test (categorical data, specifying frequencies in percent).b)Subjective and functional performance of surgically (two groups) and conservatively treated patients with LSS and controls without spinal impairments will be compared using multivariate general linear mixed model and Chi^2^-test (categorical data, specifying frequencies in percent).c)Subjective and functional performance before and after the intervention(s) will be compared using multivariate general linear mixed model and Chi^2^-test (categorical data, specifying frequencies in percent).d)Associations of subjective and functional assessments will be tested by means of correlation analyses.

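### The only sample-size justification is a one-sample test of before-after ODI change in fusion patients; it gives no power for early versus later rehabilitation or for decompression versus fusion, the stated aims.

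*Protocol article*

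**What the plan says.** The abstract gives the purpose as to "evaluate the impact of post-operative rehabilitation timing as well as surgical intervention type on psychometric properties and functional outcomes". Section 2.3.7, analysis (a), carries this out: "Subjective (ODI, SF-12) and functional performance (handgrip strength, FRT) of early and later post-operative rehabilitation intervention groups will be compared". Section 2.3.8 adds that surgical patients are randomised to an early or delayed start, or choose one if they decline randomisation.

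Section 2.3.6 sets the size. "The ODI was set as our primary outcome measure", and "the ODI results of 46 patients with LSS (41% men) who underwent fusion surgery were used". The effect size is a change within patients: "Considering the mean change from baseline of 16.1 points and the standard deviation of 17.8, a large effect (d = 0.9) can be expected". At 5% significance and 95% power, with the test named as a "one-sample *t*-test", "the minimum sample size needed with this effect size is 15 patients with LSS who will undergo fusion surgery". The section then allows for about two thirds of patients reaching the minimum clinically important difference and for 20% dropout, and arrives at 30 patients in each group. It does not say which groups are meant. It states no difference between groups and makes no two-sample calculation.

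**The concern.** A one-sample test on change from baseline asks whether fusion patients improve on average. Early and later rehabilitation patients have all had surgery, so the average improvement is common to both arms and does not indicate how far the arms differ. The same holds for decompression against fusion, and the cohort used contains no decompression-only patients. Multiplying a one-sample number by the number of groups does not produce a two-sample design, and neither does dividing it by a responder share.

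At stake is how the main comparison will be read. Section 2.3.6 is the only basis given for the group size, and the only power figure in it is 95%. A reader who attaches that figure to the timing comparison would take a non-significant result as much stronger evidence of no difference than the design can give.

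**Working it through.** **Inputs from section 2.3.6:** mean change 16.1, SD 17.8, alpha 5%, power 95%, n = 15, responder share 65% (about two thirds), dropout 20%, 30 enrolled per group.

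**Assumptions added here:** SD 17.8 in both arms; an unadjusted, two-sided 5% t-test; a between-group difference of 10 points. The 10 points is the protocol's threshold for change within a patient; the protocol does not offer it as a target difference between groups.

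**1. The plan's own figures.** d = 16.1/17.8 = 0.904, rounded to 0.9. One-sample power comes from the noncentral t distribution with n − 1 degrees of freedom and noncentrality d√n.
- One-sided, n = 15: noncentrality 0.9 × √15 = 3.49, power 95.2%. This reproduces the stated minimum of 15.
- Two-sided, n = 15: power 90%. Two-sided, 95% would need 19 patients at d = 0.9.
- Inflation: 15/(2/3)/0.8 = 28.1, or 15/0.65/0.8 = 28.8. Either is consistent with 30 after rounding up.

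So the arithmetic is right for the test named, provided that the test is one-sided. The text does not state sidedness.

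**2. Two-sample power, 30 enrolled per timing group.** Evaluable: 30 × 0.8 = 24 per arm. Power comes from the noncentral t with 2n − 2 = 46 degrees of freedom and noncentrality (Δ/SD)√(n/2).

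| Between-group difference | Power, 24 per arm | Power, 30 per arm (no dropout) |
|---|---|---|
| 5 points | 16% | 19% |
| 8 points | 33% | 40% |
| 10 points | 48% | 57% |
| 16.1 points | 87% | 93% |

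- For 10 points at 24 per arm: noncentrality (10/17.8) × √12 = 1.95.
- Sensitivity to SD, 10 points, 24 per arm: 68% at SD 14, 62% at SD 15, 40% at SD 20.
- Detectable difference, 24 per arm: 0.826 × 17.8 = 14.7 points at 80% power; 1.063 × 17.8 = 18.9 points at 95%.
- 95% CI half-width: 2.013 × 17.8 × √(2/24) = 10.3 points; with all 30 evaluable, 9.2 points.
- Evaluable patients needed per arm for 10 points: 51 for 80% power, 84 for 95%.

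**3. If 30 applies to each timing-by-surgery cell.** Each timing arm then has 60 enrolled and 60 × 0.8 = 48 evaluable. Power is 78% for 10 points and 99% for 16.1 points. The half-width is 1.986 × 17.8 × √(2/48) = 7.2 points.

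**4. Keeping the plan's own d = 0.9 as a between-group effect.** A two-sample test at 95% power needs 34 evaluable per arm two-sided, or 28 one-sided. Twenty-four evaluable falls short on either.

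**The case against.** The strongest reply is that the protocol makes no false power statement. Section 2.3.6 attaches the 95% to 15 fusion patients and a one-sample test, and describes the sizing as approximate and hypothetical. A reader might infer that 95% power is claimed for early versus later rehabilitation, but the text does not say so. A reader might also infer that the calculation serves no planned analysis. That too is unsupported: section 2.3.7(c) plans a before-after comparison. Nor is this a miscalculation, since 15 and 30 both reproduce. These points stand. The fault is that the stated aims have no sizing of their own.

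Several limits on the size of the problem also stand. The 10-point group difference is an assumption. The groups are undefined, and the wider reading raises power to 78%. The planned mixed model, with baseline adjustment or repeated measures, could do better than an unadjusted t-test (81% for 10 points at 24 per arm if the effective SD were 12), although the sizing uses neither. It would also be too strong to say that the trial cannot exclude differences above 10 points: an estimate of zero at 24 per arm would exclude differences above 10.3, and at 30 per arm above 9.2. Patients who choose their timing would shrink a randomised-only comparison, but the documents give no share, so no figure can be attached. Finally, no section plans an equivalence conclusion; the risk lies in how readers will interpret a null result.

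None of this supplies a between-group calculation. On neither reading of the group definition does power for 10 points reach 95% under the stated assumptions.

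**Conclusion.** The concern holds as a mismatch between sizing and aim. The 95% power with n = 15 belongs to a one-sided before-after test in fusion patients, and the protocol gives no power for the timing or surgery-type contrasts. With SD 17.8 in both arms, an unadjusted two-sided 5% test and 20% dropout, power for a 10-point timing difference is 48% if 30 means each timing group (40% to 68% for SD 20 to 14) and 78% if it means each timing-by-surgery cell. On the first reading, even a timing effect as large as the whole 16.1-point before-after change has 87% power. The exact figure depends on the SD, the target difference and the group definition; the absence of any sizing for the main contrast does not.

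**What to change.** Keep the enrolment target and change the wording of section 2.3.6:

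- State that n = 15 and 95% power apply only to the one-sided before-after test in fusion patients.
- Define what each group means: timing group, surgery group, or timing-by-surgery cell.
- At the resulting evaluable number, report two-sample power and the detectable ODI difference for the timing contrast, and likewise for surgery type, with SD, dropout and target difference labelled as assumptions. The 24-per-arm figures should not be written in until the groups are defined.
- Present both contrasts as estimated differences with 95% confidence intervals, and state that a non-significant result will not be read as no difference.

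The cost is a protocol and registry wording change with no extra patients. The downside is that the stated power becomes less favourable.

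### The step from 15 to 30 patients per group counts non-responders twice, and 15 fits the named test only if it is one-sided, which is not stated

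*Protocol article*

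**What the plan says.** All the inputs stand in the protocol article, section 2.3.6 (Power analysis and sample size considerations).

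- Source cohort: "the ODI results of 46 patients with LSS (41% men) who underwent fusion surgery were used".
- Effect size: "Considering the mean change from baseline of 16.1 points and the standard deviation of 17.8", from which "a large effect (d = 0.9) can be expected".
- First result: "With a significance level of 5% and a power of 95%, the minimum sample size needed with this effect size is 15 patients". The test is named as a one-sample t-test run in G*Power. The number of tails is not given there or elsewhere in the article.
- Responder rate from the same cited study: "Only 65% (30) of the patients reduced their ODI by at least ten points one year post-operatively".
- Inflation: "Taking into account that approximately two-third of the patients included will reach the minimum clinically important difference and assuming a relatively high dropout rate". With dropout put at 20%, the section arrives at 30 patients to be enrolled in each group.

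The section describes the sample size as an approximation reached by a hypothetical approach.

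**The concern.** Two steps in this derivation need checking.

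The first is the use of the responder share as an inflation factor. A one-sample t-test on mean change uses every patient's change score. A patient who improves by 4 points contributes an observation just as one who improves by 30 does. Failing to reach 10 points is not a loss of data, unlike dropout, so enrolling more patients to make up for it has no basis in this test. If the mean and SD were computed in a cohort that included such patients, their effect on power is already in the effect size.

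The second is whether 15 is the sample size for the test as described. A 5% level without further comment is usually read as two-sided, and on that reading 15 looks too small for 95% power.

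At stake is whether the only printed justification of the sample size can be followed and defended. A reader could also take the surplus from the responder step for a deliberate margin, which it is not.

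**Working it through.** **Inputs (all from section 2.3.6).** Mean change 16.1; SD 17.8; d = 16.1/17.8 = 0.9045, printed as 0.9; alpha 0.05; power 0.95; responders 30/46 = 65.2%, used as about two-thirds; dropout 20%.

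**Step 1: reproduce 15.** Power of a one-sample t-test follows from the noncentral t distribution with n − 1 degrees of freedom and noncentrality d√n. For n = 15 and d = 0.9 the noncentrality is 0.9 × √15 = 3.486. The critical value is 1.761 one-sided and 2.145 two-sided.

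| n | One-sided power, d = 0.9 | Two-sided power, d = 0.9 | Two-sided power, d = 0.9045 |
|---|---|---|---|
| 14 | 93.8% | 87.5% | 87.8% |
| 15 | 95.2% | 90.0% | 90.2% |
| 18 | 97.8% | 94.9% | 95.1% |
| 19 | 98.3% | 96.0% | 96.1% |

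Fifteen is therefore the exact one-sided minimum. The two-sided minimum is 19 at d = 0.9 and 18 at the unrounded d = 0.9045.

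**Step 2: reproduce 30.**

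- Dropout only: 15/(1 − 0.20) = 18.75, so 19.
- Responder share of two-thirds, then dropout: 15/(2/3) = 22.5; 22.5/0.8 = 28.1.
- Responder share of 65%, then dropout: 15/0.65/0.8 = 28.8.

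The division is not written out, but the text names both reasons. Dropout alone falls 11 short of 30, while both together give 28.1 to 28.8, which rounds up to 30. The responder share was evidently applied.

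**Step 3: are non-responders already in the effect size?** The section introduces the mean, the SD and the responder rate as results from the same cited cohort of 46. The 46 − 30 = 16 patients who missed 10 points thus belong to the group that produced 16.1 and 17.8. As a consistency check, assume normally distributed changes with that mean and SD. The share improving by at least 10 points is then P(Z ≥ (10 − 16.1)/17.8) = P(Z ≥ −0.343) = 63.4%, close to the observed 65.2%. The mean and SD already imply about one-third non-responders.

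**Step 4: what the before-after test needs without the responder step.**

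- One-sided: 15/0.8 = 18.75, so 19 enrolled.
- Two-sided, d = 0.9045: 18/0.8 = 22.5, so 23 enrolled.
- Two-sided, d = 0.9: 19/0.8 = 23.75, so 24 enrolled.

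**Step 5: what 30 per group delivers.** Evaluable: 30 × 0.8 = 24. Two-sided within-group power at n = 24 and d = 0.9 is 98.8%. For a difference in mean change between two groups of 24, assuming that the SD of 17.8 holds in both, the 95% confidence interval half-width is t(0.975; 46) × 17.8 × √(2/24) = 2.013 × 5.138 = 10.3 ODI points.

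**The case against.** The strongest defence is that both printed figures can be reproduced: 15 is exact for a one-sided test, and 30 is 28.1 to 28.8 rounded up. This stands. It would be wrong to say that the numbers do not follow from the inputs; the fault lies in the reason for one step and in one unstated parameter.

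On sidedness, a one-sided test of improvement is possible, and a condensed article may leave the number of tails to a fuller document. This also stands, so the shortfall to 90% is conditional on a two-sided reading. A reader might infer that the planned analyses are two-sided and so contradict the calculation. Section 2.3.7 lists mixed models, t-tests, regressions, Chi² tests and correlations without stating sidedness, so the article does not show that conflict.

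On the responder step, a reader might infer that an analysis restricted to patients who improved is intended, since only then would non-responders be unusable. Nothing in the article plans this: items a to c of section 2.3.7 compare groups, or measurements before and after intervention, with no such restriction. It can also be argued that the Background's aim of finding predictors of success or failure justifies wanting enough responders; 24 × 2/3 = 16 would be available. That would be coherent, but section 2.3.6 states no responder target and attaches the step to a t-test on mean change.

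Finally, the error does no harm to the before-after test, because 30 exceeds the 23 to 24 needed even two-sided. This stands and limits the severity.

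**Conclusion.** The point holds as a fault in the stated derivation. Dividing by the responder share has no basis for a t-test on mean change, because the 16 non-responders are already in the mean and SD; this rests on reading 16.1 and 17.8 as results for all 46 patients, as the section presents them. The step accounts for the move from 19 to about 29, rounded to 30.

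The sidedness part is conditional. If the 5% is one-sided, 15 is right and should be labelled so. If it is two-sided, power at 15 is about 90% instead of 95%, and 18 to 19 evaluable patients are needed.

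The before-after test is not underpowered on either reading. That surplus should not be taken as evidence that the early-versus-late comparison is adequately sized, since a one-sample calculation does not address it. With 24 evaluable per group the half-width of 10.3 points, under the assumed SD, is about as large as the 10-point change the section uses as its responder threshold.

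**What to change.** In section 2.3.6:

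1. Delete the two-thirds step, so that dropout is the only inflation.
2. State whether the one-sample test is one-sided or two-sided. If two-sided, restate the within-group requirement as 19 evaluable and 24 enrolled at d = 0.9.
3. Keep 30 per group as the enrolment number and say what it delivers: about 24 evaluable per group after 20% dropout, two-sided within-group power of about 99% at d = 0.9, and a between-group 95% confidence interval half-width of about 10.3 ODI points. Declare the assumption that the SD of 17.8, taken from a fusion cohort, applies to both timing groups.

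The cost is a change of wording. The enrolment target, the assessments and the planned analyses stay as they are.
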